##### Proliferation Assays

Human PBMCs will be labelled with 5 μM carboxyfluorescein succinimidyl ester (CFSE; Invitrogen) according to the manufacturer’s instructions, and proliferation will be assessed by flow cytometry after stimulation with anti-human CD3 (OKT3; 2 μg/ml) and soluble mouse anti-human CD28 (1 μg/ml; eBioscience) for 4 days.

Alternatively cell proliferation will be assessed using the ATPLite™ Luminescence Assay System (PerkinElmer) according to the manufacturer’s instructions. Luminescence will be measured on a TopCount NXT.

##### Intracellular calcium imaging

For intracellular calcium imaging experiments lymphocytes will be isolated using magnetic-activated cell sorting. All measurements will be performed in HEPES buffer containing (in mM): NaCl, 120; KCl, 2.5; NaH2PO4, 1.25; HEPES, 30; MgSO4, 2; glucose, 10; pH 7.25 and osmolarity will be set to 305 mOsm/kg. Cells will be loaded with 5 μM Fura-2 AM (Invitrogen) for 30 min at 37 °C. Anti-mouse CD3 (clone 145-2C11; eBioscience, 10 μg/ml) will be added after 15 min and fluorescence will be measured with a TECAN infinite M200Pro fluorimeter (Tecan Group Ltd.). Excitation will be alternated between 340 and 380 nm and emission will be measured at 509 nm.

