#### Secondary endpoints

Secondary endpoints extend the already mentioned investigations in the peripheral blood and mainly focus on three points: The absolute and relative change from baseline of the aforementioned cell counts in the CSF at indicated time points of sampling (see Additional file 1: Assessment Schedule), functional characterization of T cells in peripheral blood and the CSF at indicated time points of sampling (see Additional file 1: Assessment Schedule) and the evaluation of potential neuroprotective properties of alemtuzumab. A complete listing is found in Table 4.

**Table 4 Tab4:** Secondary Endpoints

1. Absolute and relative change from baseline of cell-counts in the CSF at indicated time-points of sampling (see Additional file 1: Assessment Schedule). The same cell-types as indicated for the primary endpoints will be evaluated.	
2. Functional characterization of T-cells in the peripheral blood and the CSF at indicated time-points of sampling (see Additional file 1: Assessment Schedule):	
a. Activation status of cell surface receptors assessed by flow cytometry: Relative and absolute change from baseline of mean fluorescence intensity (MFI) and of proportion of positive cells regarding CD25, HLA-DR, LFA-1, CD29, CD69, CD71 expression	
b. Expression of co-inhibitory molecules assessed by flow cytometry: Relative and absolute change from baseline of MFI and of proportion of positive cells regarding PD-1 = CD279, ICOS = CD278, TIM-3, CTLA4 expression	
c. Effector functions of CD4 and CD8 positive T cells:	
- Relative and absolute change from baseline of the results of cell proliferation assays assessed as percentage of proliferated cells	
- Relative and absolute change from baseline of cytokine production measurement assessed as concentration	
- Relative and absolute change from baseline of cytolytic activity assessed by flow cytometry measurement of MFI and proportion of positive cells regarding Granzyme B, Perforin and CD107a expression	
- Relative and absolute change from baseline of intracellular calcium response assessed as concentration	
d. Migrational capacity:	
- Relative and absolute change from baseline MFI and proportion of positive cells assessed by flow cytometry expression analysis of CD11a, CD31, CD44, CD49d, CCR5, CCR6, CCR7	
- Absolute and relative change of cell numbers of migrated cells compared to baseline assessed in an in vitro model by flow cytometry analysis	

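### As printed, the calcium-imaging buffer contains no calcium salt, so calcium entry from outside the cell cannot contribute to a secondary endpoint defined as the general T-cell calcium response

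*Protocol article*

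**What the plan says.** The section on intracellular calcium imaging fixes the recording medium for the whole assay: "All measurements will be performed in HEPES buffer containing (in mM): NaCl, 120; KCl, 2.5; NaH2PO4, 1.25; HEPES, 30; MgSO4, 2; glucose, 10". It adds that "pH 7.25 and osmolarity will be set to 305 mOsm/kg". The indicator and stimulus follow: "Cells will be loaded with 5 μM Fura-2 AM (Invitrogen) for 30 min at 37 °C", then "Anti-mouse CD3 (clone 145-2C11; eBioscience, 10 μg/ml) will be added after 15 min". Fluorescence is read with excitation alternating between 340 and 380 nm. No calcium salt, chelator, calcium re-addition step or second medium appears, and no published method is cited for this assay.

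The assay serves one bullet of Table 4, item 2c, on the effector functions of CD4 and CD8 positive T cells: "Relative and absolute change from baseline of intracellular calcium response assessed as concentration". The table does not limit this response to calcium released from internal stores.

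**The concern.** The assay measures a rise in calcium inside the cell. Such a rise can draw on two sources: internal stores and calcium entering from the surrounding medium. If the medium has no added calcium, the second source is closed. The measured quantity is then narrower than the endpoint in Table 4.

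What is at stake is interpretation. The endpoint is one of the means by which the study asks whether alemtuzumab alters T-cell function. Under the printed recipe a change in calcium entry would not be visible, and an unchanged result could say nothing about that component. A laboratory repeating the assay from the article would inherit the same limitation without being told of it.

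**Working it through.** No sample-size or error-rate arithmetic applies. The check sets the two places side by side and then asks whether the only stated figure on the buffer settles the matter.

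**1. What the recipe contains.** Section on intracellular calcium imaging: NaCl 120, KCl 2.5, NaH2PO4 1.25, HEPES 30, MgSO4 2 and glucose 10 mM. Calcium salts listed: none. Added extracellular calcium as printed: 0 mM. Because no chelator is listed, the accurate term is nominally calcium-free.

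**2. Scope of the recipe.** The section applies it to all measurements and describes no step at which calcium is supplied later. The stimulus is the only addition described after dye loading.

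**3. What the endpoint asks for.** Table 4, item 2c, asks for change from baseline in the calcium response, with no restriction to one source.

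**4. Comparison.** With no added calcium outside the cell, entry cannot contribute meaningfully. Step 1 therefore yields a narrower quantity than step 3. This follows from the composition alone and needs no outside figure.

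**5. Does the stated osmolarity show whether a salt was left off the list?** Ideal sum, concentration times number of particles:

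2×120 + 2×2.5 + 2×1.25 + 30 + 2×2 + 10 = 240 + 5 + 2.5 + 30 + 4 + 10 = 291.5 mOsm.

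This is 305 − 291.5 = 13.5 below the stated value. Bringing HEPES to pH 7.25 adds sodium equal to 30 / (1 + 10^(pKa − 7.25)) mM. The pKa is not in the documents; an assumed range of 7.3 to 7.55 gives:

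| Assumed pKa | Added Na+ (mM) | Total as listed | Total with an assumed 2 mM CaCl2 (+6) |
|---|---|---|---|
| 7.3 | 14.1 | 305.6 | 311.6 |
| 7.55 | 10.0 | 301.5 | 307.5 |

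The list as printed can reach about 305 without a calcium salt. The sums are ideal values, and the osmolarity is in any case adjusted to its target. The figure neither proves nor excludes an omitted salt and is not used as evidence here.

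**The case against.** **The article is a condensation.** The strongest reply is that this is one paragraph in a journal article, the full protocol is not shown, and a calcium salt may simply have dropped out of the list. The article nowhere calls the assay calcium-free. This stands as a limit on certainty: it cannot be said that the laboratory in fact worked without calcium. It does not remove the point. The article did not leave the buffer to another document. It printed a recipe down to 1.25 mM phosphate, applied it to every measurement and cited no source from which a missing component could be recovered. If calcium was dropped by accident, the published method is wrong and needs correcting.

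**Stronger readings a reader might infer, which the documents do not support:**

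- *That most of the T-cell calcium response is lost.* The documents do not say how the response divides between entry and store release, so no share can be given.
- *That the loss affects all 15 patients at every visit.* The sampling times are in the assessment schedule (Additional file 1), which is not shown, and the sample-size section itself considers samples from only 10 patients.
- *That the gap up to 305 mOsm/kg reveals a missing calcium salt.* Sodium from pH adjustment can account for it.
- *That the endpoint cannot be reported as a concentration because no calibration is described.* Dual-wavelength readings can be converted to concentration by calibration, and an article may leave that laboratory detail to the full protocol.

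**The stimulus is a separate matter.** The calcium assay names an anti-mouse CD3 clone, whereas for the proliferation assay "proliferation will be assessed by flow cytometry after stimulation with anti-human CD3 (OKT3; 2 μg/ml") is specified, and the suppression assay uses the same anti-human antibody. That inconsistency could put even the store-release signal in doubt and needs its own reconciliation. Resolving it would leave the buffer unchanged.

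**Conclusion.** The point holds in a limited form. As printed, the medium for all calcium measurements has no calcium salt and no re-addition step, so entry from outside the cell cannot contribute, while Table 4, item 2c, defines the response without that restriction. Recipe and endpoint do not match.

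The conclusion rests on one assumption, that the assay is run as the article describes it. If calcium is present in the working buffer, the defect shrinks to an error in the published recipe, which still needs correcting. If the calcium-free condition is intended, the defect lies in the endpoint's wording.

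Severity is minor. One of four bullets under item 2c of a long secondary list is affected, in a study that treats its inference as exploratory and hypothesis-generating. No primary endpoint, precision calculation, eligibility rule or safety assessment depends on it. The size of the lost signal cannot be estimated from the documents.

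**What to change.** The investigators should first say whether calcium was left off the printed list or is deliberately absent. Then one of three changes applies:

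1. If calcium was omitted in error, correct the recipe and state the extracellular calcium concentration.
2. If both components are of interest, specify a two-step assay, with stimulation in calcium-free buffer followed by calcium re-addition, and report release and entry separately.
3. If the calcium-free condition is intended as it stands, redefine this bullet of Table 4, item 2c, as calcium release from internal stores only.

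Whichever applies, the same medium should be used at baseline and at follow-up, because the endpoint is a change from baseline. The cost is at most one reagent and a wording change in the method or the table; the two-step option also adds a re-addition step and a second reading per run. There is no added burden on patients.

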##### Suppression Assay

CD4^+^CD25^+^CD127^dim/-^ regulatory T cells will be separated from responder T cells by magnetic-activated cell sorting using a CD4^+^CD25^+^CD127^dim/-^ Regulatory T Cell Isolation Kit II (Miltenyi Biotec). Responder T cells will be labelled with 5 μM carboxyfluorescein succinimidyl ester (CFSE; Invitrogen) according to the manufacturer’s instructions. Afterwards regulatory T cells and CFSE^+^ responder T cells will be cocultured at a ratio of 1:2 and 1:1. Cultures will be stimulated with anti-human CD3 (OKT3; 2 μg/ml) and soluble mouse anti-human CD28 (1 μg/ml; eBioscience) for 4 days. Proliferation will be assessed by flow cytometry after stimulation.

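### The calcium assay's only listed stimulus is labelled anti-mouse CD3, although its endpoint concerns human T cells and the sister assays use anti-human CD3

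*Protocol article*

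**What the plan says.** All references are to the protocol article.

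- **Endpoint.** Table 4, item 2 is headed "Functional characterization of T-cells in the peripheral blood and the CSF at indicated time-points of sampling". Under 2c, on the effector functions of CD4 and CD8 T cells, one bullet reads "Relative and absolute change from baseline of intracellular calcium response assessed as concentration".
- **Calcium assay.** The section Intracellular calcium imaging begins "For intracellular calcium imaging experiments lymphocytes will be isolated using magnetic-activated cell sorting". After the buffer and the dye loading it gives the stimulus: "Anti-mouse CD3 (clone 145-2C11; eBioscience", at 10 μg/ml. No other stimulus and no positive control is listed. The buffer is given as sodium chloride, potassium chloride, sodium phosphate, HEPES, magnesium sulphate and glucose.
- **Sister assays.** Under Proliferation Assays, "proliferation will be assessed by flow cytometry after stimulation with anti-human CD3 (OKT3; 2 μg/ml". Under Suppression Assay, "Cultures will be stimulated with anti-human CD3 (OKT3", with the same clone at the same concentration.

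**The concern.** A functional T-cell readout needs a stimulus that engages the receptor on the cells being tested. Here the cells are human, but by its own label the named antibody is directed at mouse CD3. If the laboratory follows the text, endpoint 2c compares calcium signals across visits without a stimulus aimed at the human receptor. Any difference, or lack of one, then cannot be attributed to T-cell receptor signalling after alemtuzumab.

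The protocol's Discussion treats the functional properties of T cells after treatment as a main line of enquiry. Material is also scarce once lymphocytes are depleted, so cells spent on an unsuitable stimulus may be hard to replace for that visit.

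**Working it through.** The point rests on a comparison of sections, not on a calculation.

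**1. Species of the cells.** The calcium section does not state the species. Table 4, item 2 does so in effect, by placing the T cells in participants' blood and CSF. The article also says that samples from other patient cohorts and from healthy individuals may serve as controls, and these are human too. No mouse lymphocytes are assayed in this trial; work on mice appears only as cited literature.

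**2. The three CD3-stimulated assays side by side.**

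| Section | Cells | CD3 antibody as written | Concentration |
|---|---|---|---|
| Proliferation Assays | human PBMCs | anti-human, OKT3 | 2 μg/ml |
| Suppression Assay | sorted regulatory and responder T cells | anti-human, OKT3 | 2 μg/ml |
| Intracellular calcium imaging | magnetically sorted lymphocytes | anti-mouse, 145-2C11 | 10 μg/ml |

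Target species, clone and concentration all differ in the third row, so a different reagent is specified.

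**3. Could the label mean an antibody raised in mice?** No. In the proliferation and suppression assays the CD28 antibody is described as a mouse antibody against human CD28. The authors therefore distinguish host from target species, and here the target is given as mouse.

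**4. Does anything else in the section supply a human-directed stimulus?** No. The anti-mouse antibody is the only one listed.

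**5. Scarcity of material.** Inputs are 90 ml of blood (Cell Isolation) and assumed mean lymphocyte counts of 2100 cells/μl before and 100 cells/μl after treatment (Sample size). With 90 ml = 90,000 μl and no loss during isolation, so that these are upper bounds on average yield:

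- before treatment: 90,000 × 2100 = 189 million lymphocytes
- after treatment: 90,000 × 100 = 9 million lymphocytes

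These cells are shared among many assays.

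**6. The plan's own figures.** The precision statements under Sample size do not bear on this point. They reproduce with half-width = t(0.975, n−1) × SD/√n × √(χ²(0.80, n−1)/(n−1)):

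| SD (cells/μl) | n = 15: computed (stated) | n = 10: computed (stated) |
|---|---|---|
| 450 | 283.7 (284) | 375.4 (375) |
| 50 | 31.5 (32) | 41.7 (42) |
| 500 | 315.3 (315) | 417.2 (417) |

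**The case against.** The strongest objection is that the text supports only a mismatch of labels. A reader might infer that the calcium response would be about zero at every visit for all 15 patients, and that an unchanged result would then pass for preserved T-cell signalling. The documents support neither step. They give a species label and a clone name, and are silent on cross-reactivity with human CD3. If the stimulus did nothing, the baseline run would probably already show no rise after the antibody is added, and the failure would be noticed. With a baseline response near zero, relative change would be unstable or undefined, not a clean null. This part of the objection stands.

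It can also be said that the sentence may have been carried over from mouse work while the laboratory uses a human-reactive antibody. That is plausible, and the document cannot settle it. It does not remove the point: the article positively states a reagent that conflicts with its own endpoint and its own sister assays, which differs from leaving a detail to a fuller protocol.

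On the buffer, the objection largely succeeds. A condensed method may omit an addition made during recording, and calcium release from internal stores could still register without external calcium. The missing salt is a query, not a second error.

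Finally, the reach is small: one bullet among many secondary endpoints, in a study that declares its inference exploratory and sets no significance level.

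**Conclusion.** The point holds in this limited form. The calcium assay as written has no stimulus directed at human CD3, so the change from baseline in calcium response under endpoint 2c could not be interpreted as a T-cell receptor response. This follows from the antibody's stated target, the human origin of the cells, and the absence of any other stimulus in the section. It assumes that the label is accurate and that the text describes what will be done.

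The size of any distortion cannot be computed from the document. Severity is moderate: one exploratory secondary sub-endpoint is affected, and the primary endpoints and the sample-size reasoning are not.

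**What to change.** 1. Confirm with the laboratory which CD3 antibody is used, or has been used, in the calcium assay.
2. In Intracellular calcium imaging, replace the anti-mouse clone with an anti-human CD3 antibody consistent with Proliferation Assays and Suppression Assay, and state the concentration that applies to this assay.
3. Treat any results already obtained with the anti-mouse clone as not valid for endpoint 2c, and say so in the report.
4. As a clarification only, state whether the recording buffer contains calcium and, if so, at what concentration.

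The cost is a confirmation and a short text correction. A human-directed antibody is already specified for two other assays, and neither sample size, visits nor patient procedures change. The timing is favourable: recruitment is described as ongoing, and PBMCs for work other than immune cell composition are frozen for at least 4 weeks before analysis. If samples have already been run with the wrong clone, repeating them depends on stored aliquots, and the article does not say whether any would remain.

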##### Cytokine detection

Appropriate ELISA-Kits (enzyme linked immunosorbent assay) will be used to detect cytokine concentrations in cell culture supernatants and cerebrospinal fluid. Alternatively fluorescent bead immunoassays (FlowCytomix, eBioscience) will be used to quantify the production of the chemokines and cytokines according to the manufacturer’s instructions.

##### Suppression Assay

CD4^+^CD25^+^CD127^dim/-^ regulatory T cells will be separated from responder T cells by magnetic-activated cell sorting using a CD4^+^CD25^+^CD127^dim/-^ Regulatory T Cell Isolation Kit II (Miltenyi Biotec). Responder T cells will be labelled with 5 μM carboxyfluorescein succinimidyl ester (CFSE; Invitrogen) according to the manufacturer’s instructions. Afterwards regulatory T cells and CFSE^+^ responder T cells will be cocultured at a ratio of 1:2 and 1:1. Cultures will be stimulated with anti-human CD3 (OKT3; 2 μg/ml) and soluble mouse anti-human CD28 (1 μg/ml; eBioscience) for 4 days. Proliferation will be assessed by flow cytometry after stimulation.

##### Concentration of Neurotrophic Factors

Investigation of the concentration of the following neurotrophic factors in peripheral blood and cerebrospinal fluid: nerve growth factor (NGF), brain-derived neurotrophic factor (BDNF), neurotrophin-3 (NT-3), and neurotrophin-4 (NT-4), ciliary neurotrophic factor (CNTF).

Cell culture supernatants and CSF will be interrogated for neurotrophins by appropriate ELISA kits according to manufacturer’s instructions.

##### Quantification of markers of neurodegeneration

Appropriate ELISA kits will be used to detect S100β, Tau, phospho-Tau, β-Amyloid, Neurofilament (low weight), Neurofilament (high weight), N-acetylaspartate (NAA), Tubulin, Actin, neuron-specific enolase (NSE) and glial fibrillary acidic protein (GFAP).

##### Multi-electrode Array

To analyse the impact of cell culture supernatants or cerebrospinal fluid on activity of neuronal networks, different parameters of neuronal network activity will be determined using the multi-electrode array technique [36–38]. Multi-electrode array detects compound field potentials in the spatial vicinity of multiple extracellular electrodes in densely cultured hippocampal neurons, which are capable of generating spontaneous synchronized activity. A complete listing is found in Table 5.

**Table 5 Tab5:** Additional Endpoints

The following additional endpoints will undergo exploratory evaluation:	
1. Number of patients who experienced sustained accumulation of disability (SAD) during the study period (Study period: From the day of treatment initiation until month 36 visit. SAD: for patients with a Baseline EDSS score of 0.0, SAD is defined as an increase of ≥1.5 points sustained over a 6-month consecutive period. For patients with a Baseline EDSS score of ≥1.0, SAD is defined as an increase of ≥1.0 point sustained over a 6-month consecutive period.)	
2. Time to SAD	
3. Time to sustained reduction in disability (SRD) based on EDSS scores (SRD: a ≥1 point decrease on the EDSS sustained for 6 consecutive months for patients with a baseline EDSS ≥2)	
4. Absolute Number of relapses during the study period	
5. Number or relapses which occurred during the study period and required corticosteroid therapy	
6. Proportion of patients who are relapse free at year 3	
7. Time to first relapse	
8. Absolute and relative change from baseline in the following functional scores at each time point of assessment after treatment initiation (see Additional file 1: Assessment Schedule): EDSS, visual functional system score as part of the assessments for EDSS, MSFC and each MSFC component, FSMC and each subscore (mental and physical fatigue)	
9. The proportion of patients who have worsened, remained stable, or improved as indicated by change from Baseline in EDSS scores at the end of the study	
10. Change from baseline of the following HRQoL measures at each time point of assessment after treatment initiation (see Additional file 1: Assessment Schedule): FAMS, EQ-5D (total score, Physical Component summary Measure, Mental Component Summary Measure), SF-36	
11. The proportion of patients who have worsened, remained stable, or improved as indicated by change from Baseline in MSFC scores at the end of the study	
12. Absolute and relative change from baseline amplitudes [V] and latencies [s] of evoked potentials (VEP, SEP, MEP)	
13. Percent change from baseline in magnetic resonance imaging (MRI)-T2 hyperintense lesion volume at each time point of assessment after treatment initiation (see Additional file 1: Assessment Schedule)	
14. Number of new gadolinium-enhancing lesions on MRI-T1 in comparison to Baseline	
15. Number of new or enlarging hyperintense lesions measured by T2-weighted MRI in comparison to Baseline at each time point of assessment (see Additional file 1: Assessment Schedule)	
16. Absolute and relative change from baseline of IL-21 concentration in blood serum at indicated time-points of sampling	
17. Absolute and relative change from baseline of following parameters assessed in CSF: cell counts, concentration of lactate, protein, and immunoglobulines (IgA, IgG, IgM)	
18. Qualitative assessment of the change in presence of oligoclonal bands in CSF from baseline	
19. Proportion of patients with no MS disease activity (i.e., deterioration in MRI related endpoints, relapse) at the end of the study	

At our study center samples of highly controlled and validated groups of other MS therapy cohorts (e.g. natalizumab and fingolimod) and other neuroimmunological diseases (NMO, CIDP, autoimmune encephalitis) and healthy sex- and age-matched individuals are available as control groups. These control groups will be used for experiments, whenever it is possible and reasonable.

